# OBJECTIVES

To investigate whether adjusting the length of the BP-limb of the OLGB based on measured total small bowel length leads to more weight loss, resolution of co-morbidities with less development of micronutrient deficiencies and bowel movements compared a to a standard limb length in OLGB in patients using a standardized multivitamin supplement (FitForMe Primo).

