**Secondary Objective(s):**

1) To compare the percent of total weight loss (%TWL) between the groups at 1,2,3 and 4 years.

2) To compare the percent excess weight loss (%EWL) between the groups at 1,2,3, 4 and 5 years.

Definition: %EWL (Initial Weight – Postop Weight) / (Initial Weight – Ideal Weight)

(ideal weight is defined by the weight corresponding to a BMI of 25 kg/m2 )

3) To compare the percent excess BMI loss (%EBMIL) between the groups at 1,2, 3, 4 and 5 years.

Definition: %EBMIL (ΔBMI / (Initial BMI – 25)) * 100)

4) To compare the proportion of patients with 22 ≤ BMI ≤ 30 between the groups at 1,2 3, 4 and 5 years.

5) To compare the mean number of daily bowel movements and number of days with daily bowel movements > 3 in the last two weeks, between the groups at 6 months, 1,2, 3, 4, and 5 years.

6) To compare the Quality of life measured by the RAND-36 questionnaire between the groups at 6 months, 1,2, 3, 4 and 5 years, absolute and compared to before surgery

7) To compare the percentage of patients experiencing moderate to severe dumping symptoms defined by the Dumping Severity Score (DSS) (see Emous et al.) at 6 months, year 1, 2, 3, 4 and 5 between the groups, absolute and compared to before surgery.

8) To compare the proportion of patients in the two groups who have neither deficiencies of iron, nor vit. D, nor vit B12 without extra suppletion, at 6 months, 1, 2, 3, 4 and 5 years. Deficiencies are defined by the lower border of the local normal laboratory values.

9) To compare the proportion of patients in the two groups who have a deficiency at 6 months, 1, 2, 3, 4 and 5 years, or received extra suppletion for :

- Vitamin B1

- Vitamin B6

- Folic acid

- Vitamin A

- Vitamin D

- Calcium

- Phosphate

- Albumin

- Zinc

- Copper (visit 1,3,5 years)

- Selenium (visit 1,3,5 years)

Deficiencies are defined by the lower border of the local normal laboratory values.

10)To compare the proportion of patients between the groups at 1, 2, 3, 4 and 5 years without diabetes, both those with remission of diabetes and those without de novo diabetes, defined as an HbA1c less than 48 mmol/mol without diabetes medication in the last 6 months. ^#^

11) To compare the proportion of patients between the groups at 1, 2, 3,4 and 5 years with improvement of diabetes, defined as a reduction of HbA1c with at least 10 mmol/mol, but not reaching remission criteria and/or less anti-diabetic medication ^#^.

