12) To compare the proportion of patients between the groups at 1, 2, 3, 4 and 5 years with remission of hypertension, defined as a blood pressure of 140/90 mmHg or less without antihypertensive medication ^#^.

13) To compare the proportion of patients between the groups at 1, 2, 3, 4 and 5 years with improvement of hypertension, defined as a lower blood pressure of at least 10 mm Hg systolic and/or 5 mmHg diastolic, and/or less antihypertensive medication (not reaching the criterion of remission) ^#^.

14) To compare the proportion of patients between the groups at 1, 2, 3, 4 and 5 years with resolution of sleep apnea, defined by cessation of CPAP or other devices use, documented by their own pulmonologist

15) To perform analysis of the above parameters in the subgroups with TSBL 500-700 and >700.

16) To compare within the standard group of patients with an allocated BP-limb length of 150 cm those with a TSBL < 500 to those with a TSBL 500-700 and to those with TSBL >700 cm on the above mentioned parameters.

^#^ : patients are asked to bring along with their visit an overview of current medication from their local pharmacist and actual use will be checked with the patient. In case of absence of the overview, after informed consent is given, the local pharmacist will be asked to provide the investigator with an overview of the medication

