# STUDY POPULATION

## Population : patients from the Centrum Obesity North-Netherlands (CON), who comply with the IFSO criteria during a multidisciplinary screening and have chosen to have a primary mini-GB (OLGB) and are willing to participate.

## Inclusion criteria

In order to be eligible to participate in this study, a subject must meet the following criteria:

- Age between 18 and 65
- BMI > 40 kg/m^2^ or
- BMI > 35 kg/m^2^  with co-morbidity : diabetes, hypertension, OSAS, arthrosis
- Willing to participate with written informed consent before start of the surgery
- A completely measured total small bowel during surgery
- No pre-operative deficiencies of vit B_12_, vit D and iron, measured with ferritin
- No use of extra (multi-)vitamin supplements with exception of vit D max 800 IU/day
- Able to swallow the multivitamin FFM WLS primo (tested before surgery)

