### Secondary study parameters/endpoints

1) Percent of total weight loss (%TWL) at 1,2,3,and 4 years.

2) Percent excess weight loss (%EWL) at 1,2,3, 4 and 5 years.

Definition: %EWL (Initial Weight – Postop Weight) / (Initial Weight – Ideal Weight)

(ideal weight is defined by the weight corresponding to a BMI of 25 kg/m2 )

3) Percent excess BMI loss (%EBMIL) at 1,2,3, 4 and 5 years.

Definition: %EBMIL (ΔBMI / (Initial BMI – 25)) * 100]

4) Proportion of patients with 22 ≤ BMI ≤ 30 Kg/m^2^ at 1,2,3, 4 and 5 years

5) Mean number of daily bowel movements in the last two weeks at 6 months, 1,2,3, 4 and 5 years.

6) Mean number of days with daily bowel movements > 3 in the last two weeks at 6 months, 1,2,3, 4 and 5 years.

6) Quality of life measured by the RAND-36 questionnaire at 6 months, 1,2,3, 4 and 5 years, absolute and compared to before surgery.

7) percentage of patients experiencing moderate to severe dumping symptoms defined by the Dumping Severity Score (DSS) at 6 months, 1,2,3, 4 and 5 years, absolute and compared to before surgery.

Moderate to severe is defined as 3 or more dumping symptoms with a severity score of 2 or 3 on a 4-point Likert scale. Symptoms are divided in two categories, e.g. early and late,

as described by Emous et.al. (7)

8) percentage of patients who have neither deficiencies of iron, nor vit. D, nor vit B12 without extra suppletion, at 6 months, 1,2,3, 4 and 5 years . Deficiencies are based on the local normal laboratory values.

9) Proportion of patients who have a deficiency at 6 months, 1,2,3, 4 and 5 years, or received extra suppletion for:

- iron (ferritin)

- vitamin B_12_

- vitamin D_3_

- Vitamin B_1_

- Vitamin B_6_

- Folic acid

- Vitamin A

- Vitamin D

- Calcium

- Phosphate

- Albumin

- Zinc

- Copper at 1,3 or 5 years

- Selenium at 1,3 or 5 years

10)Proportion of patients at 1,2,3, 4 and 5 years without diabetes, both with remission and without de novo, defined as an HbA1c less than 48 mmol/mol without diabetes medication in the last 6 months.

11)Proportion of patients at one year and two years with improvement of diabetes, defined as a reduction of HbA1c of 10mmol/mol or more but not reaching remission criteria and/or less anti-diabetic medication.

12)Proportion of patients at 1,2,3, 4 and 5 years with remission of hypertension, defined as a blood pressure of 140/90 mmHg or less without antihypertensive medication.

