## Secondary study parameter(s)

All secondary endpoint parameters (quantitative and qualitative) will be presented as described in section : Patient demographics other baseline characteristics.

For the evaluation of differences between groups, the primary analysis approach will be applied for the quantitative secondairy endpoint parameters..

For the qualitative parameters a Fisher exact test or a Chi-square test will be used.

For the parameters related to the occurrence of side effects, the evaluation focusses on the “absence” of differences. For these analysis estimates of risk differences with 90% confidence intervals, based on the Farrington-Manning Method will be used (non-inferiority setting, one sided approach). Due to sample size constraints, formal hypothesis tests on non-inferiority will not be performed. Multivariable logistic (or log-binomial) regression modelling is not foreseen.

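### The diabetes endpoint (item 10) pools remission with absence of new diabetes, so it does not isolate diabetes resolution and dilutes any remission effect

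*Protocol*

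**What the plan says.** Section 7.1.2 (Secondary study parameters/endpoints), item 10, sets one proportion at years 1 to 5: patients "without diabetes, both with remission and without de novo, defined as an HbA1c less than 48 mmol/mol without diabetes medication in the last 6 months". Section 2, secondary objective 10, compares the same proportion between arms, "without diabetes, both those with remission of diabetes and those without de novo diabetes", by the same HbA1c and medication criterion.

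The general aim in section 2 is to learn whether adjusting the limb "leads to more weight loss, resolution of co-morbidities with less development of micronutrient deficiencies".

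Section 4.2 (Inclusion criteria) does not require diabetes. One route is "BMI > 40 kg/m^2^ or", with no further condition. The other is a BMI above 35 "with co-morbidity : diabetes, hypertension, OSAS, arthrosis", so diabetes is one of four alternatives.

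Item 11, the only other diabetes endpoint apart from HbA1c as a routine laboratory value, counts improvement and leaves out patients who reach remission.

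Section 9.2 (Secondary study parameter(s)) says: "For the qualitative parameters a Fisher exact test or a Chi-square test will be used". Logistic or log-binomial modelling is not planned; that remark closes the paragraph on side effects.

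**The concern.** A patient without the disease cannot resolve it. Under item 10, a participant with no diabetes at entry normally meets the success criterion before surgery and goes on meeting it unless diabetes develops. Such patients raise the proportion in both arms and say nothing about remission.

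No other part of the protocol supplies the missing comparison. Item 11 excludes remission, and is itself hard to read without a remission rate beside it, because an arm with more remissions has fewer patients left to count as improved. Objectives 15 and 16 split by small bowel length only. The evaluation over strata in section 9.1, which mentions co-morbidities, is described for the primary parameter, and section 9.2 carries the primary approach over only to quantitative endpoints.

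At stake is whether the planned analysis answers the co-morbidity part of the aim. A real difference in remission would be reported as a much smaller difference between two high percentages. A difference in new diabetes could add to it or cancel it.

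**Working it through.** **The plan's own figures.** The protocol states no prevalence, remission rate or expected difference for this endpoint, so there is none to reproduce. The only figure borrowed is 92 per arm from section 4.4. That figure checks for its own purpose: a 5-point difference with SD 12 in both arms gives power of 80.3% at 92 per arm, and 88.9% with SDs of 12 and 9 (the protocol states 80% and 88.8%).

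**Inputs assumed here.** Baseline diabetes prevalence p = 15%, 25% or 35%. Remission among diabetics r0 = 60% (standard) and r1 = 80% (adjusted), chosen only for illustration. New diabetes among non-diabetics d = 0 in both arms at first.

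**Step 1: what the pooled proportion contains.** In each arm P = p·r + (1 − p)(1 − d). With equal p in the arms,

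P1 − P0 = p(r1 − r0) − (1 − p)(d1 − d0).

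If d is also equal, the second term vanishes and the pooled difference is exactly p times the remission difference. This proportionality holds on the risk-difference scale. The odds ratio also shrinks, but not in proportion (at p = 30%, 2.14 pooled against 2.67 among diabetics).

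**Step 2: size and expected z at 92 per arm.** Pooled: z = (P1 − P0) / √{[P0(1 − P0) + P1(1 − P1)]/92}. Diabetics only: z = 0.20 / √{[0.24 + 0.16]/(92p)}.

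| p | Pooled rates | Pooled difference | z pooled | Diabetics per arm | z diabetics only |
|---|---|---|---|---|---|
| 15% | 94% v 97% | 3 points | 0.98 | 13.8 | 1.17 |
| 25% | 90% v 95% | 5 points | 1.29 | 23.0 | 1.52 |
| 35% | 86% v 93% | 7 points | 1.56 | 32.2 | 1.79 |

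For p = 25%: pooled SE = √[(0.0900 + 0.0475)/92] = 0.0387, and 0.05/0.0387 = 1.29. Diabetics only: SE = √(0.40/23) = 0.1319, and 0.20/0.1319 = 1.52.

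**Step 3: does pooling ever gain power here?** With no new cases, the ratio of squared z (pooled to diabetics only) is Σ(1 − r)r / Σ(1 − r)[1 − p(1 − r)], summed over the two arms. Since 1 − p(1 − r) is never below r, the ratio never exceeds 1. With all 106 randomised per arm and p = 30%, power is 33% pooled and 41% among diabetics. A 2% rate of new diabetes in both arms leaves the 6-point difference as it is and lowers pooled power to 30%.

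**Step 4: unequal rates of new diabetes.** Take p = 25%.
- Remission 60% v 80%, with new diabetes 2 points higher in the adjusted arm: 5 − 0.75 × 2 = 3.5 points.
- Equal remission, with new diabetes 2 points lower in the adjusted arm: 0 + 0.75 × 2 = 1.5 points.

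The single proportion cannot show which component produced the difference.

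**The case against.** **The composite is deliberate.** The proportion free of diabetes among all randomised patients counts cure and prevention together, and can be interpreted. That stands: item 10 is neither an error nor an internal contradiction. But it is not a measure of resolution, which the aim names, and no other endpoint fills that place.

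**The statistical analysis plan could report the components.** It could, since the wording names both. But the protocol defines one proportion with one criterion in two places, so a remission comparison would be a new endpoint and not an elaboration of this one.

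**The gain is modest and every rate is assumed.** This stands. All the z values are below 1.96 under either analysis. The case rests on what is estimated and not on power.

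A reader might also infer three stronger points, which the documents do not support.
- *That the result is mainly chance imbalance in baseline diabetes.* At p = 25% and 92 per arm, the SD of the difference in prevalence is √(2 × 0.25 × 0.75/92) = 6.4 points. An extra diabetic lowers the pooled rate only if not in remission, so this enters multiplied by 0.2 to 0.4, or 1.3 to 2.6 points. Splitting each arm's variance as p·r(1 − r) + (1 − r)²p(1 − p), the imbalance part is 14% to 36% over the rates used here, and the pooled z already includes it. Non-diabetics dominate the level of the proportion but not the difference between arms.
- *That the trial will be unable to give a remission rate.* HbA1c and medication are recorded at visits, and medical history, medication and baseline values of endpoints are to be tabulated. The data will exist; the prespecified comparison does not.
- *That items 12 to 14 share the problem.* They speak of remission or improvement of hypertension and of stopping CPAP or other devices, which presuppose the condition. Item 12 reads "with remission of hypertension, defined as a blood pressure of 140/90 mmHg or less without antihypertensive medication" and has no clause on new disease. Stating those denominators is routine detail.

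**Conclusion.** The point holds for item 10 and secondary objective 10. As defined, the endpoint does not isolate resolution of diabetes, and the listed endpoints contain no comparison of remission among patients who had diabetes at baseline.

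The algebra of the dilution is exact for the risk difference when prevalence and the rate of new diabetes are equal in the arms. The sizes (20 points reported as 3, 5 or 7) rest on the assumed prevalences and remission rates and on no new cases; other rates would change them. Pooling brings no gain in power to set against the loss of meaning, though a diabetics-only comparison would be underpowered too. If new diabetes differs between arms, the pooled figure mixes two effects.

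This concerns one secondary endpoint. The primary endpoint and its sample size are untouched. It is worth correcting because the correction is cheap and is best made before allocation is unsealed for the yearly interim analyses.

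**What to change.** In item 10 and secondary objective 10, replace the single proportion with two endpoints:
- 10a: remission, by the HbA1c and medication criterion already given, among patients with diabetes at baseline;
- 10b: new diabetes among patients without diabetes at baseline.

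State how baseline diabetes status is determined from the baseline data. The pooled proportion may stay as a descriptive summary.

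The change is to wording only. Medical history, medication and baseline endpoint values are already planned, and item 11 needs a baseline HbA1c in any case. The price is smaller denominators and wider intervals in points. In the 25% example with 92 per arm, the 95% half-width is 1.96 × 0.1319 = 25.8 points around a 20-point difference among diabetics, against 1.96 × 0.0387 = 7.6 points around a 5-point pooled difference. Relative to the effect being estimated, the first is the more precise (25.8/20 = 1.29 against 7.6/5 = 1.52).

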### Other study parameters

Measurements of CRP, hemoglobin, WBC, thrombocytes, sodium, potassium, creatinine, BUN, ASAT, ALAT, alkaline phosphatase, yGT, HbA1c are part of routine investigation in the follow-up and will also be part of the study

Serum will be stored for analysis in later stage in case of new developments or insights relevant for the study become evident.

## Randomisation, blinding and treatment allocation

After informed consent is given, the patient is asked to swallow one Fitforme WSL primo capsule. A patient who is not able to swallow the capsule will be withdrawn form the study.

Randomization is performed using a table of random figures delivered by a independent party (clinical pharmacist), using envelopes with the treatment allocation.

The envelope contains a study number on the outside and the same number with one of the treatment arms within. The envelope will be opened by the OR nurse when the surgeon has succeeded in measuring the TSBL.

If the surgeon is not able to measure the TSBL the patient will be withdrawn from the study.

The study number and the patients medical file number will be forwarded to the principle investigator by the surgeon.

The surgeon will document the allocation, total small bowel length and length of the BP-limb in the file containing only study numbers. In the follow-up neither any of the usual care medical providers nor the patient is aware of the allocation or BP-limb length. The surgeon will not describe the TSBL and the BP-limb length in his surgical report.

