# INTRODUCTION AND RATIONALE

Omega-loop gastric bypass, also known as mini-gastric bypass (OLGB/MGB) is currently one of the most effective treatment options for morbid obesity. It is technically a more simple procedure compared to the RYGB and has proven in some studies to have a better outcome in terms of weight loss and reduction of co-morbidities.

The aim of the weight loss surgery is to achieve an optimum weight loss aiming at a BMI of 25 kg/m^2^ in combination with a minimum of side effects, like vitamin, macronutrient, mineral deficiencies and diarrhea.

There is substantial variation in the determination of the biliopancreatic (BP) limb length with some surgeons using a fixed length and some a length based on the initial BMI. The length varies between less than 150 cm to more than 250 cm. A recent retrospective study by Charalampos et.al. adjusting limb length from 200 to 300 cm depending on BMI resulted in on average comparable EWL when corrected for initial BMI. The average BMI after 36 months was 27.5 Kg/m2 (± 5.3). This strategy of BP based on initial BMI results in 16% of patients with a final BMI > 33 and 16% with less than 22.

Furthermore despite the advice to take life-long (over-the-counter) multivitamin suppletion 20% or more patients developed de novo deficiencies of iron, vit B12, vit D, and/or minerals in the first postoperative year (1).

Ahuja et.al. adjusted the limb length from 150 to 250 cm depending on BMI and also found increasing number of deficiencies of micro-nutrients with increasing BP length (2). In this study patients were advised to use a multivitamin supplement, however no specific brand was used.

Some evidence exists in RYGB surgery that the length of the BP-limb influences weight loss. Nergaard et al. performed a RCT comparing a RYGB with a BP-limb of 200 to 60 cm with a RYGB with an alimentary limb of 60 and 150 cm respectively. The longer BP-limb length led to more weight loss but also to more bowel movements and micronutrient deficiencies (3). Total small bowel length was measured in their whole patient population and varied between 480 and 870 cm but was not taken in to account in terms of stratification.

Zorilla et.al performed a systematic review on limb length in RYGB and found 13 studies meeting adequate quality (4). Weight loss on the whole was better in patients with longer BP limbs.

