# STUDY DESIGN

This is a double-blind randomized 5 year study with two arms. Patients who are scheduled for primary OLGB surgery are eligible when during the surgery total small bowel length can be measured and when they are able to swallow the Fitforme WLS primo multivitamin capsule. Patients will be allocated to one of the two surgical treatment arms by randomization at the beginning of the operation. Only the operating surgeon is aware of the allocation and will document total small bowel length, treatment allocation and BP-length in a coded database. Both the TSBL and the length of the BP-limb will not be documented in the patient file. The investigators and the patient will not be informed on the BP-limb length during the study.

Patients with a small bowel that could not be measured during surgery will be treated according to the current daily practice and will not enter the study.

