# TREATMENT OF SUBJECTS

Patients will be randomly allocated to one of the two treatment arms :

- 1. A standard BP-limb length of 150 cm
- 2. A BP-limb length depending on total small bowel length (TSBL) measured during the surgical procedure :
- TSBL : < 500 cm : 150 cm
- TSBL : 500-700 cm : 180 cm
- TSBL : > 700 cm : 210 cm

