## Study procedures

A standard operation protocol for OLGB will be used in all patients. The pouch will be made with the help of a linear stapler. At first, the stomach will be transected horizontally at the junction of the corpus and antrum at the level of crow’s foot. A small pouch is made with help of a calibration sonde of 34 French, the pouch is finished near the angle of His. Then the total limb length is measured. With a succesfull TSBL measurement the OR nurse will open the envelop and the allocated procedure will be communicated to the surgeon. Based on the randomization outcome biliopancreatic limb length is measured. In case the measurement of the total limb length does not succeed, standard limb length of 150 cm is performed. An antecolic, retrogastric anastomosis is performed by liniar stapling and the remaining defect is closed by V-loc. An anti-reflux stitch is performed. Integrity of the anastomoses is checked by methylene-blue-test and in case of leakage, extra sutures will be applied. The mesenterial defect of Peterson will be closed as far as possible by endo hernia stapling or unresolvable V-loc.

The extra measurements of limb length will take less than ten minutes of time. In patients allocated to standard treatment the surgeon will construct a BP-limb of 150 cm. In patients allocated to the adjustment length, the length of the BP-limb will depend on the total small bowel length : < 500 cm : 150 BP; 500-700 cm : 180 BP and > 700 cm : 210 BP.

On leave of the hospital the patients will be provided with Fitforme WSL Primo multivitamin capsules for the following period and will be instructed to use one capsule once daily.

Follow-up will take place in accordance with usual care, i.e. after 1,6,12 and 24 months and yearly up till 5 years. Extra visits will be at 18,30,42 and 54 months for compliance check and distribution of FFM multivitamins.

Weight measurements and blood samples will be taken in accordance with the standard protocol of follow-up after bariatric surgery in our institute added with 20 ml for selenium and copper measurements and future lab tests at 1,3 and 5 years.

Data from 6,12 and 24 months and every year thereafter up to five years after surgery will be anonymously collected in a database.

At each visit standard care includes :

- inquiry after well being and complaints, side effects, adverse events
- documenting current medication use, both regular and over-the-counter, and when applicable CPAP use

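### TSBL class is known before the envelope is opened and sets the limb length in the adjusted arm, yet neither the randomisation nor the primary test uses it: some precision is lost, with no bias

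*Protocol*

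**What the plan says.** **Allocation method.** Protocol, Randomisation, blinding and treatment allocation: "Randomization is performed using a table of random figures delivered by a independent party (clinical pharmacist), using envelopes with the treatment allocation". No stratification factor or block is named there or elsewhere in the Protocol.

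**Order of events.** The same section says "The envelope will be opened by the OR nurse when the surgeon has succeeded in measuring the TSBL". Study procedures agrees: "With a succesfull TSBL measurement the OR nurse will open the envelop and the allocated procedure will be communicated to the surgeon". Study design differs: "Patients will be allocated to one of the two surgical treatment arms by randomization at the beginning of the operation".

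**Role of TSBL.** In Treatment of subjects, one arm has "A standard BP-limb length of 150 cm" and the other "A BP-limb length depending on total small bowel length (TSBL) measured during the surgical procedure": 150 cm below 500 cm, 180 cm for 500-700 cm, 210 cm above 700 cm. Secondary objective 15 is "To perform analysis of the above parameters in the subgroups with TSBL 500-700 and >700". The introduction remarks that in an earlier randomised trial in RYGB, TSBL was measured but "was not taken in to account in terms of stratification".

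**Primary analysis.** Statistical analysis, Primary study parameter(s), specifies a two-sample t-test, or a Mann-Whitney test if the data are skewed, without covariates. The homogeneity analysis names gender, baseline BMI, co-morbidities and compliance as examples. TSBL is not among them.

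**The concern.** TSBL is the covariate on which the trial is built. It determines whether a patient in the adjusted arm receives 0, 30 or 60 cm more limb than the same patient would in the standard arm, and the rationale supposes that it influences weight loss and deficiencies. The surgeon records it in the coded study file for both arms, and by the two procedural sections it is known before allocation is revealed. Using it would therefore cost very little.

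At stake is precision. If TSBL predicts %TWL, an unadjusted comparison leaves that variation in the error term, and a given trial may by chance have more long bowels in one arm. The reader would then have to weigh an observed imbalance in the central covariate with no prespecified analysis that deals with it.

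**Working it through.** **Inputs from the Protocol.** Difference 5, SD 12 in each arm (9 in the adjusted arm as the alternative), two-sided alpha 0.05, 92 evaluable and 106 randomised per arm (Sample size calculation). TSBL median 690 cm, SD 94 cm (Introduction). **Assumptions.** TSBL is normally distributed. Mean %TWL differs by D = 5 points between TSBL above 700 cm and the rest, with D from 2 to 8 as the range. The Protocol gives no figure for D.

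**1. The plan's own figure.** SE = 12 × √(2/92) = 1.77; noncentrality 5/1.77 = 2.83; the t-test has 80.3% power (plan: 80%). With SDs of 12 and 9, power is 88.9% (plan: 88.8%). The plan's figures are reproduced.

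**2. Class shares.** Under Normal(690, 94): below 500 cm 2.2%, 500-700 cm 52.1%, above 700 cm 45.8%. The introduction also reports 2-3% below 400 cm, against 0.1% under this curve, so the lowest class may be larger than 2%.

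**3. Chance imbalance.** With p = 0.458 and 106 per arm, the SD of the between-arm difference in share is √(2 × 0.458 × 0.542/106) = 0.068. P(difference exceeds 0.10) = P(|Z| > 1.46) = 14.4%. The 95% range is ±1.96 × 0.068 = ±13 percentage points. Simulating 100,000 unstratified allocations of 212 patients gave 14.5% for a difference of at least 10 points. The sex-specific distributions (41% of women and 63% of men above 700 cm) change the SD only to 0.067 and 0.066.

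**4. Effect on the primary contrast and on power.** The 95% bound on the shift is 1.96 × 0.068 × D. The share of the outcome variance due to class is p(1−p)D²/12². The residual SD after adjustment is 12 × √(1 − that share). Power is for a difference of 5 at 92 per arm.

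| Assumed D (points of %TWL) | 95% bound on shift, 106 per arm | Variance share | Residual SD | Power with TSBL class in the model |
|---|---|---|---|---|
| 2 | 0.27 | 0.7% | 11.96 | 80.5% |
| 5 | 0.67 | 4.3% | 11.74 | 82.0% |
| 8 | 1.07 | 11.0% | 11.32 | 84.6% |

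**5. Is the shift an extra error?** At D = 5 its variance is (0.068 × 5)² ≈ 0.117. The variance of the unadjusted difference at 106 per arm is 2 × 144/106 = 2.72. The ratio, 0.117/2.72 = 4.3%, is exactly the variance share in step 4. The shift is a component of the existing standard error and adds nothing to it.

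**6. Planned subgroups.** About 0.52 × 92 = 48 and 0.46 × 92 = 42 evaluable patients per arm give 52% and 47% power for 5 points. Of 212 patients about 97 would have TSBL above 700 cm. Simple randomisation would put 39 to 58 of them in an arm (95% range). Even a 39/58 split raises the SE only by √(1/39 + 1/58)/√(2/48.5) = 1.02, or 2%.

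**The case against.** The strongest reply is that nothing here is wrong. Unstratified 1:1 randomisation with an unadjusted test is a valid design. The SD of 12 is a total SD, so it already contains whatever TSBL contributes. That stands, and it rules out several stronger readings:

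- A reader might infer that the primary comparison is biased, or that 0.7 points must be added to its error. Step 5 shows otherwise. The 0.7 is also a 95% bound, not a maximum.
- A reader might infer that 92 per arm is too few for want of stratification. The stated figure holds without it.
- A reader might infer that imbalance in TSBL confounds objective 15. That objective compares the arms within a TSBL class, so the mix of classes cannot confound it. Stratified blocks would only even out the arm sizes, a small gain by step 6.
- A reader might take the introduction's remark on the earlier trial as a commitment to stratify. It describes another trial, with fixed limb lengths, and commits this one to nothing.

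It also stands that TSBL sets the limb length in the adjusted arm only, that the 5-point class effect has no source in the Protocol (the introduction says the contribution of residual bowel length has not been studied in OLGB), and that details of strata or blocks could sit in a document not at hand.

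Other provisions cover the point only in part. The baseline section allows methods to be modified if differences look clinically relevant, but that decision follows sight of the data. The list of homogeneity factors is open-ended, but homogeneity of effect is a different question. The look after 50 patients at the number with TSBL below 500 cm in the intervention arm shows that the TSBL mix is thought to matter, but it does not balance or adjust anything. None of this replaces a primary comparison that names TSBL in advance.

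**Conclusion.** The point holds as an improvement, not as an error. The Protocol has a central baseline covariate available before allocation is revealed and uses it in neither the randomisation stated nor the primary test stated. Type I error, unbiasedness and the sample size are unaffected. The gain forgone is modest: power of about 82% instead of 80.3% at 92 per arm if TSBL class shifts %TWL by 5 points, and between 80.5% and 84.6% for 2 to 8 points. If TSBL does not predict %TWL, the gain is essentially nil. The imbalance figure (more than 10 percentage points in about 14% of trials) rests on the normal approximation to the cited TSBL distribution. Most of the benefit comes from adjustment, which needs no change to the envelopes.

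Separately, the Protocol contradicts itself on timing: Study design places randomisation at the start of the operation, while the two procedural sections place the opening of the envelope after the measurement. Stratified envelopes are possible only if the envelope is drawn after TSBL is known.

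**What to change.** 1. **Primary study parameter(s).** Prespecify the primary comparison of %TWL at 5 years as adjusted for TSBL (class or continuous), for example a linear model with arm and TSBL. Fix this before any unblinded look. TSBL is already recorded for both arms, so the only cost is the wording.
2. **Randomisation, blinding and treatment allocation, if enrolment is still open.** Have the clinical pharmacist prepare separate concealed envelope series for TSBL up to 700 cm (merging the rare class below 500 cm for randomisation only) and above 700 cm. Use varying, undisclosed block sizes. Choose the series after TSBL is recorded. Because study numbers are forwarded to the principal investigator, number the envelopes so that they do not reveal the series.
3. **Study design.** Reconcile the time of randomisation with the two procedural sections.

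Item 2 costs one extra envelope series. It carries a small risk of taking an envelope from the wrong series, and makes allocation slightly more predictable for the surgeon, who learns every allocation and judges whether the measurement succeeded. If enrolment has closed, item 1 alone secures most of the gain.
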